## Abstract

**Background:**

Cognitive Behavioural Therapy for psychosis (CBTp) has an established evidence base and is recommended by clinical guidelines to be offered during the acute phases of psychosis. However, few research studies have examined the efficacy of CBTp interventions specifically adapted for the acute mental health inpatient context with most research trials being conducted with white European community populations.

**Aims:**

The aim of this study is to conduct a pilot randomised controlled trial (RCT), which incorporates the examination of feasibility markers, of a crisis-focused CBTp intervention adapted for an ethnically diverse acute mental health inpatient population, in preparation for a large-scale randomised controlled trial. The study will examine the feasibility of undertaking the trial, the acceptability and safety of the intervention and the suitability of chosen outcome measures. This will inform the planning of a future, fully powered RCT.

**Methods:**

A single-site, parallel-group, pilot RCT will be conducted examining the intervention. Drawing on principles of coproduction, the intervention has been adapted in partnership with key stakeholders: service users with lived experience of psychosis and of inpatient care (including those from ethnic minority backgrounds), carers, multi-disciplinary inpatient clinicians and researchers. Sixty participants with experience of psychosis and in current receipt of acute mental health inpatient care will be recruited. Participants will be randomly allocated to either the crisis-focused CBTp intervention or treatment as usual (TAU).

**Discussion:**

Findings of this pilot RCT will indicate whether a larger multi-site RCT is needed to investigate the efficacy of the intervention. If the initial results demonstrate that this trial is feasible and the intervention is acceptable, it will provide evidence that a full-scale effectiveness trial may be warranted.

**Trial registration:**

This trial has been prospectively registered on the ISRCTN registry (ISRCTN59055607) on the 18th of February 2021.

## Introduction

Cognitive Behavioural Therapy for psychosis (CBTp) is a psychological therapy which targets the distress relating to experiences of psychosis by adapting the way an individual thinks and behaves. Although there have been recent reviews challenging the effectiveness of CBTp [21, 22], the evidence base generally demonstrates that CBTp is an effective intervention, with a small to medium effect size, in improving outcomes for people experiencing psychosis [46, 52]. CBTp is recommended by clinical guidelines, such as the National Institute of Health and Clinical Excellence [30], to be offered in the acute phase of psychosis, i.e. in inpatient settings. However, despite this recommendation, the majority of the research examining the effectiveness of CBTp has been done with outpatient community samples or in outdated inpatient settings. These settings are not reflective of the current inpatient context, which have a higher threshold for admission and care for more ethnically diverse service users [19, 49].

It is well demonstrated that the acute stage is an important time to intervene psychologically as this is when people are in most need of psychological support; are often at risk to themselves (e.g. self-harm or suicide), to (e.g. violence and aggression) and/or from (e.g. exploitation) others; and are experiencing distressing symptoms of psychosis [45]. The average stay on an acute mental health inpatient ward in England is 31 days [28]; therefore, there is ample time to offer a psychological intervention which is brief, targeted to the crisis and adapted to meet the needs of this population [7]. There is evidence that cognitive behavioural interventions can be adapted to be delivered as a brief intervention, i.e. within 6–8 sessions [14, 41], and are suitable for inpatients [41]. Therefore, an inpatient admission may be a time where people could engage in and derive benefit from a psychological intervention [11].

There is an overrepresentation of inpatient service users from ethnic minority backgrounds, with those from black African and black Caribbean backgrounds being four times more likely to be compulsorily detained compared to their white counterparts [29]. There is evidence that service users from ethnic minority backgrounds are less likely to be offered psychological therapies, have more negative experiences of mental health services [17] and have poorer outcomes following a mental health crisis [11]. Therefore, it is essential that acute inpatient psychological interventions are also developed to meet the needs of ethnic minority groups to be useful and acceptable in this setting. There is some existing evidence that CBTp can be culturally adapted to be appropriate for ethnic minority populations; however, this research has not been undertaken with inpatient populations [15, 37].

Three recent systematic reviews have been conducted to examine the feasibility, acceptability and effectiveness of cognitive behavioural psychological interventions for people in acute mental health inpatient settings [19, 34, 49]. They have demonstrated some initial promise with small improvements in psychotic symptoms at the end of therapy, but not at longer-term follow-up [34, 49]. There is also initial evidence that psychological therapy may have a small effect on readmission, depression and anxiety [19]. However, all reviews agreed that the quality of research was poor to moderate and that the majority of psychological therapies had not been specifically adapted for delivery in the acute mental health inpatient setting, or focused on the current mental health crisis [49]. This is a strong indication of a need for a robust evaluation of a psychological intervention, such as CBTp, adapted for the current acute mental health inpatient setting with a focus on crisis reduction.

An adapted crisis-focused CBTp intervention for inpatient settings, which is culturally competent, has been developed following best practice guidelines from the Medical Research Council (MRC) on complex intervention development [42]. The CBTp intervention was developed from several sources of information including a systematic review [49], relevant psychological theory [8, 26], core competency frameworks for working with people experiencing psychosis [38], and acute mental health inpatient care respectively [51], three qualitative interview studies [47, 48, 50], a Delphi study [27] and additional stakeholder consultation as outlined in the methodology.

The aim of this study is to conduct a pilot randomised controlled trial, which includes examination of feasibility markers, of the outlined adapted crisis-focused CBTp intervention for acute inpatients experiencing psychosis. More specifically, this study will:Assess the feasibility of conducting the RCT (examined by the number of service users who give informed consent as a proportion of the number identified as eligible, recruitment timeframe, the number of service users randomised, number of participants who drop out from the trial, number of post-therapy and follow-up assessments completed and participant qualitative feedback regarding the research process).Examine the acceptability of the intervention:To service user participants (examined by the number of therapy sessions attended, number of sessions declined or not attended, number of people who declined therapy once randomised, therapy modules/resources used, mode of therapy, location of therapy sessions, number of sessions conducted prior to discharge, time and duration of sessions, qualitative feedback on the intervention)To therapists (examination by therapists’ fidelity, therapist experience of the training intervention and delivery of therapy)Examine the safety of the intervention through the monitoring of adverse eventsExamine the suitability of the outcome measures to examine the efficacy of the interventions, in preparation for a fully powered effectiveness RCT

## Methodology

### Design

This study will adopt a single-centre, individually randomised, parallel-group, RCT design with an embedded qualitative component. Participants will be randomly allocated to either treatment as usual (TAU) or CBTp plus TAU in a 1:1 ratio, as undertaken in other psychological therapy trials conducted in inpatient settings [20, 36]. Outcome measure assessments will be carried out at baseline, 2 months post-randomisation and 6 months post-randomisation either face to face or remotely. Relapse, rehospitalisation and adverse event data will be again examined 12 months post-randomisation. This protocol is reported following guidance from the SPIRIT tool (Standard Protocol Items: Recommendations for Intervention Trials, [10]). The trial has been registered on the ISRCTN trial registry (ISRCTN59055607). The study plan is outlined in Fig. 1 and the schedule of participant activities is in Table 1. Full Health Research Authority (HRA) and NHS Research Ethics Committee (REC) approval has been granted (IRAS ID: 272043; 20/LO/0137/AM01) and the study is sponsored by the University College London.

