### Sample size

We will aim to recruit sixty participants in line with recommendations by Consolidated Standards of Reporting Trials (CONSORT) for feasibility and pilot RCTs [13], thirty of which will be randomly allocated to the therapy arm and thirty to the TAU arm. A sample of sixty is deemed of sufficient size to examine the aims of the study. Data (relevant means and standard deviations) from this study will be used to inform a power calculation for a future larger multi-site trial. The sample size will also allow for dropouts, which are common in clinical trials in acute mental health inpatient settings. Some studies report attrition rates of over 50% [36], and recruiting a larger sample will still allow us to collect adequate data to inform a larger multi-site trial.

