### Procedure

Participants will be recruited from three male acute wards, three female acute wards, three acute wards for older adults and one male psychiatric intensive care unit (PICU) in North East London NHS Foundation Trust (NELFT). The study will be advertised to the inpatient staff teams who will in turn provide information about the study to eligible participants. Due to the high turnover in acute mental health inpatient wards, inpatient staff will advertise the research to service users as early as the first day on the ward, if appropriate to do so. If participants consent, they will be contacted by a research assistant within 72 h who will share more detailed information and gain informed consent if the service user wants to participate. The research assistant will undertake all clinician-administered and self-report measures with the participant (see Table 1). Once complete, the research assistant will inform the PI of the participant number who will randomise the participant to either the CBTp intervention or TAU. The PI will inform the participant of their allocation. The research assistant will then complete further assessment sessions with all participants at 2 months post-randomisation and 6 months post-randomisation. Relapse, rehospitalisation, and adverse event data will be collected at 12 months, which does not involve contact with the participant.

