#### Feasibility criteria

The trial of the CBTp intervention will be deemed feasible if the following criteria, determined by examining published CBTp trials, are met [19, 49]:Retention rate of 75% at 2 months post-randomisation and 60% at 2 months post-randomisationRecruitment of ≥80% of the target sample size (*n* = 60) over the 12-month recruitment periodQualitative data from service users and therapists support the intervention/indicate that the intervention is acceptable.

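### The feasibility criteria date both retention thresholds (75% and 60%) at 2 months, so the 60% is redundant and the scheduled 6-month assessment has no threshold

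*Protocol article*

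**What the plan says.** The article sets one decision rule for the pilot, under Feasibility criteria: "The trial of the CBTp intervention will be deemed feasible if the following criteria, determined by examining published CBTp trials, are met". Three criteria follow, on retention, recruitment and qualitative acceptability. The retention criterion reads "Retention rate of 75% at 2 months post-randomisation and 60% at 2 months" post-randomisation, so both percentages carry the same date. The recruitment criterion accepts 80% or more of the target of 60.

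The schedule is described differently elsewhere. Design states: "Outcome measure assessments will be carried out at baseline, 2 months post-randomisation and 6 months post-randomisation either face to face or remotely". Procedure has the research assistant "complete further assessment sessions with all participants at 2 months post-randomisation and 6 months post-randomisation". Table 1 marks all eight listed scales at both the 2-month and the 6-month follow-up. For the last time point, Procedure says: "Relapse, rehospitalisation, and adverse event data will be collected at 12 months, which does not involve contact with the participant".

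No section gives a retention threshold for 6 months. The Introduction's aims, the Feasibility outcomes section and the Analysis plan provide for counting dropout, completed assessments, attrition and missing data, but attach no threshold to them.

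**The concern.** Two thresholds for one visit do no more than the higher one. The second threshold is therefore wasted, and the visit it most plausibly belonged to is left out of the rule. Six months is the last time point that needs contact with the participant, so it is the last at which retention in the ordinary sense can be lost.

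Feasibility is the purpose of this pilot, and retention is one of only three criteria that decide it. The Analysis plan also intends to rehearse the definitive trial's regression models on outcomes at the follow-up time points, so 6-month completeness bears directly on that trial's design. If the line stays as it is, the pilot can be declared feasible on retention with no test at its longest assessed follow-up. If it is corrected only after the data are seen, the visit to which the 60% applies could be chosen in the light of the result.

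**Working it through.** The thresholds are stated and not derived, so the plan has no calculation to reproduce. The check is to write the rule out literally, turn it into counts, and see what it can and cannot register.

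**Inputs from the article**
- Thresholds: 75% and 60%, both at 2 months (Feasibility criteria).
- Criteria applied jointly (Feasibility criteria).
- Participant assessments after baseline: 2 and 6 months (Design, Table 1, Procedure).
- Target N = 60. The smallest number that meets the recruitment criterion is 0.80 × 60 = 48.

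**Assumptions**
- The denominator for retention is the number randomised.
- Retention is binomial with a common true rate p. The article gives no expected 6-month rate, so p is varied from 50% to 70%.

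**Step 1: counts.** The smallest passing count is the threshold times N, rounded up.

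| Randomised | 75% | 60% |
|---|---|---|
| 60 | 0.75 × 60 = 45 | 0.60 × 60 = 36 |
| 48 | 0.75 × 48 = 36 | 0.60 × 48 = 28.8, so 29 |

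**Step 2: the literal rule.** Let X2 and X6 be the numbers assessed at 2 and 6 months. With N = 60 the text requires X2 ≥ 45 and X2 ≥ 36. This reduces to X2 ≥ 45, so the 60% has no effect. X6 does not appear. A trial with X2 = 45 meets the criterion for every possible X6.

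**Step 3: the rule if the 60% belongs to 6 months.** This is an assumption about intent. The rule becomes X2 ≥ 45 and X6 ≥ 36. A trial that just passes at 2 months could then lose at most 45 − 36 = 9 more participants by 6 months. With N = 48 the margin is 36 − 29 = 7.

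**Step 4: how often a 6-month threshold would be missed.** With N = 60, P(miss) = P(X6 ≤ 35) = 1 − P(X6 ≥ 36), where X6 ~ Binomial(60, p).

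| True 6-month retention p | P(X6 ≥ 36) | P(miss) |
|---|---|---|
| 50% | 0.078 | 0.92 |
| 55% | 0.259 | 0.74 |
| 60% | 0.556 | 0.44 |
| 65% | 0.829 | 0.17 |
| 70% | 0.964 | 0.04 |

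With N = 48 and a threshold of 29, P(X6 ≥ 29) is 0.097, 0.539, 0.794 and 0.943 at p = 50%, 60%, 65% and 70%. The threshold is therefore missed with probability 0.903, 0.461, 0.206 and 0.057. The picture is the same at the smaller size.

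Under the written rule, the probability of failing because of the 6-month count is 0 in every row. Such a trial could fail on retention only through its 2-month count.

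**The case against.** The strongest reply is that this is almost certainly a slip of one digit. Two falling percentages and two scheduled visits point to 60% at 6 months, and most readers would correct it silently. That is a reasonable guess, but the article does not confirm it. A progression rule should not depend on the reader's guess, least of all once results are known.

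Three stronger readings are tempting, and the article does not support them.

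- **That the rule contradicts itself at 2 months**, so that 36 to 44 of 60 both passes and fails. The two thresholds are joined by a conjunction and the criteria must be met. A count in that band therefore fails. The 60% is redundant, not conflicting. For the same reason, comparing the pass rate of a 75% rule with that of a 60% rule at 2 months shows little: a stand-alone 60% rule at 2 months is neither what the text says nor what it probably means.
- **That all later loss is ignored.** Dropout, attrition, completed assessments and missing data by arm will be recorded and described, and the Trial Steering Committee can advise on modifying or stopping the trial. What is missing is a 6-month threshold in the decision rule, not information about 6-month retention.
- **That the Sample size section shows heavy loss to be expected after 2 months.** It says "Some studies report attrition rates of over 50% [36"], but gives no time point. Loss of that size by 2 months would be caught by the 75% threshold. The sentence does not show how much loss would fall between 2 and 6 months.

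It is also fair to say that the feasibility analysis is descriptive and that the correction changes neither data nor sample size. This limits the cost of the error but does not make the line correct.

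**Conclusion.** Wrong as written. The retention criterion assigns both thresholds to the 2-month visit, which makes the 60% redundant and leaves the scheduled 6-month assessment outside the rule. With 60 randomised, 45 assessed at 2 months meets the criterion whatever happens by 6 months.

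The size of the gap depends on true 6-month retention, which the article does not give. Over the assumed range of 50% to 70%, a 60% threshold at 6 months would be missed with a probability falling from 0.92 to 0.04. The gap therefore matters a great deal if 6-month retention is near or below 60%, and little if it is 70% or more. These figures rest on binomial retention, a denominator of all randomised, and the unconfirmed assumption that the 60% was meant for 6 months. The defect in the wording rests on none of them.

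**What to change.** Correct the retention line under Feasibility criteria so that each threshold belongs to one scheduled assessment: 75% at 2 months post-randomisation and, if that was the intent, 60% at 6 months. State that both must be met and that the denominator is the number randomised. In counts this is at least 45 and at least 36 if 60 are randomised, or at least 36 and at least 29 if 48 are. If the 60% was not meant for 6 months, delete it and say explicitly whether 6-month retention has a threshold. Make the correction before follow-up results are examined.

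The cost is one line of text. No data are added, because the 6-month assessment is already scheduled. The downside is that the corrected criterion is harder to meet than the literal one.

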**Fig. 1 Fig1:**
[figure not shown]
Diagram of the study flow

**Table 1 Tab1:** Schedule of events

	Enrolment	Baseline	Allocation	2-month FU	6-month FU	12-month FU
**Eligibility screen**	**X**					
**Informed consent**	**X**					
**Intervention allocation**			**X**			
**Outcomes**						
PANSS-P		**X**		**X**	**X**	
BDI-7		**X**		**X**	**X**	
BHS-9		**X**		**X**	**X**	
GAD-7		**X**		**X**	**X**	
QPR		**X**		**X**	**X**	
CRISP		**X**		**X**	**X**	
GAF		**X**		**X**	**X**	
TAG		**X**		**X**	**X**	
Relapse				**X**	**X**	**X**
Rehospitalisation				**X**	**X**	**X**
Adverse events^a^				**X**	**X**	**X**
**Qualitative interviews**^b^				**X**		

*BDI-7* Beck Depression Inventory, *BHS-9* Beck Hopelessness Scale, *CRISP* Crisis Scale in Psychosis, *GAD-7* Generalised Anxiety Disorder Measure, *GAF* Global Assessment of Functioning, *PANSS-P* Positive and Negative Syndrome Scale—Positive Subscale, *QPR* Process of Recovery Questionnaire, *TAG* Threshold Assessment Grid, *FU* follow-up

^a^Adverse events will be monitored at each time point and at every therapy session

^b^Will occur 4–8 weeks post-intervention completion

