#### Crisis-focused CBTp intervention

The trial intervention will be delivered by psychological therapists working in the acute inpatient services. All therapists are clinical psychologists or counselling psychologists registered with the UK Health and Care Professions Council [HCPC], with experience of delivering CBTp in inpatient settings.

The crisis-focused CBTp intervention is underpinned by a modularised CBTp protocol that aims to deliver approximately six to eight sessions of therapy to participants. The protocol includes seven modules; engagement, assessment and identifying priorities; formulation of the crisis; stabilisation and safety; coping, self-management and problem solving; crisis plans and crisis cards; change strategy work focusing on crisis appraisals and safety behaviours; and discharge, relapse planning and recovery toolkits. The first two modules (engagement, assessment and identifying priorities, and formulating the crisis) are essential components of the intervention and the remaining ones are collaboratively chosen based on the participant’s priorities. The number of sessions will be determined by the collaborative priorities set by the service user and therapist and the length of admission, and therefore, more or less sessions can be offered. The therapy will also include at least one follow-up session post-discharge to ensure support through the discharge process. The intervention will also include strategies to involve the individual’s network, e.g. family sessions, and formulation sharing with the multi-disciplinary team.

The sessions will be delivered in a private and quiet room on the inpatient ward or outside/off the ward if the participant has the appropriate leave, e.g. in a room off the ward but on the grounds of the hospital. If the participant is discharged before therapy is complete, the sessions will continue and be delivered in community settings or remotely (e.g. via phone or video conferencing technology). This is to ensure that there is continuity in sessions post-discharge.

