### Outcomes

#### Feasibility outcomes

Individual patient data will be collected on a pre-developed sheet adhering to CONSORT guidelines [6, 39]. This will include the patient eligibility status, number of referrals received by ward staff, willingness of participants to consent, willingness of participants to be randomised and attrition. Therapy-specific data will include the number of sessions attended, number of sessions declined or not attended, number of people who declined therapy once randomised, therapy resources used, mode of therapy, location of therapy sessions, number of sessions conducted prior to and post-discharge, time and duration of sessions, quantity of homework completed and any serious adverse events. Patient outcome measure completion will also be examined.

An individual patient demographics sheet will be used to collect sociodemographic and service user data, in order to identify the types of people willing to take part in such a trial.

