### Analysis plan

The study will follow best practice guidance for the reporting of feasibility RCTs (CONSORT, [13, 39]). The focus of the analysis will be on key indicators of feasibility, including participant recruitment, retention and acceptability of the intervention, which will be summarised descriptively using frequencies and percentages. Continuous clinical outcome measures will be summarised separately by study arm using means and standard deviations or medians and interquartile ranges, as appropriate for the distribution of the data. Binary outcome measures will be summarised using frequencies and percentages. The quantity of missing data for each clinical outcome will be examined and likewise summarised by study arm. This pilot study will not have sufficient power to assess the effectiveness of the intervention. However, to trial the analysis envisaged for a future, fully powered, effectiveness RCT, clinical outcomes at follow-up time points will be compared between study arms, using linear or logistic regression models as appropriate, and adjusting for the baseline measure of the outcome in question.

The qualitative interviews will be audio recorded, transcribed verbatim and analysed using thematic analysis [9] by LW on NViVo [33]. The thematic analysis will be conducted from a critical realist position and will combine inductive and deductive approaches, seeking both to explore participants’ experiences of receiving or delivering CBTp and to answer questions about the acceptability and feasibility of the therapy, its components and its mode of delivery. Initially, each transcript will be read and reread to ensure the researcher is fully immersed in the data, and then initially coded. Codes will be collated together across interviews and grouped together to form analytical themes. Patterns of themes will be explored across the data set focussing on both commonalities and variations and comparing service user and therapist perspectives. The theme structure will be checked with a small number of participants to check it reflects their experiences. The final theme structure will also be discussed with the research team and stakeholder group (including people with lived experience of psychosis and inpatient admission).

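### Adverse events have an extra collection route in the CBTp arm, and the protocol does not say that the by-arm summary keeps it apart, so that summary is open to ascertainment bias

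*Protocol article*

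**What the plan says.** Table 1 (Schedule of events) marks adverse events at the 2-, 6- and 12-month follow-ups. Its footnote adds: "Adverse events will be monitored at each time point and at every therapy session".

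The Design section gives the arms: "Participants will be randomly allocated to either treatment as usual (TAU) or CBTp plus TAU in a 1:1 ratio". Trial therapy sessions therefore exist in one arm only. The section on the crisis-focused intervention says that its protocol "aims to deliver approximately six to eight sessions of therapy to participants", and allows more or fewer.

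Under Feasibility outcomes, the list of therapy-specific data ends with "time and duration of sessions, quantity of homework completed and any serious adverse events".

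The Clinician/researcher-rated measures section, which falls under Clinical outcomes, says that participants' clinical records will be searched for the number of serious incidents and adverse events. It draws no distinction by arm. The Procedure section adds: "Relapse, rehospitalisation, and adverse event data will be collected at 12 months, which does not involve contact with the participant".

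On analysis, the protocol says that "clinical outcomes at follow-up time points will be compared between study arms, using linear or logistic regression models as appropriate", with adjustment for the baseline measure. It names no dedicated safety comparison.

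**The concern.** Safety of the intervention is one of the four stated aims and is to be examined by monitoring adverse events. The Trial Steering Committee watches the same events and considers whether the trial should continue, be modified or be stopped. If one arm is asked more often, it will tend to show more events even when the true rates are equal.

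Two features add to this. The extra route runs through therapists, who know the allocation, whereas the research assistants are blind. The Sample size section also expects substantial dropout, citing attrition above 50% in some studies. A TAU participant who misses the follow-up interviews leaves only the clinical record, while a CBTp participant may already have been asked at several sessions.

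An apparent excess of this kind could colour the committee's view of the intervention and the safety assumptions carried into the larger trial. The inequality lies in data collection, so a later analysis plan cannot undo it unless each event's source was recorded at the time.

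**Working it through.** The protocol gives no adverse event rate, capture rate or safety figure, so there is nothing to reproduce. The check has three parts.

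**1. Scheduled occasions per arm** (Table 1; intervention section)

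- TAU: 3 (2, 6 and 12 months).
- CBTp: 3 + 6 = 9 to 3 + 8 = 11.
- The 12-month collection involves no participant contact. Leaving it out, scheduled direct contacts are at most 2 in TAU against 8 to 10 in CBTp.

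These are occasions, not amounts of information. A record review can look back over a whole interval, so the ratio of occasions is not the ratio of expected counts.

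**2. Illustrative size if all sources are pooled**

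Let s be the share of events caught by the sources common to both arms, and q the share of the remaining events caught at sessions. Both are assumptions. With equal true rates,

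apparent CBTp:TAU ratio = [s + (1 − s)q] / s = 1 + q(1 − s)/s.

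| s | q | ratio |
|---|---|---|
| 1.0 | any | 1.00 |
| 0.9 | 0.5 | 1 + 0.5 × 0.1/0.9 = 1.06 |
| 0.7 | 0.25 to 0.75 | 1.11 to 1.32 |
| 0.6 | 0.5 | 1 + 0.5 × 0.4/0.6 = 1.33 |

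A harsher assumption of s = 0.5 gives 1.25 to 1.75 for the same range of q, which shows how far the result is driven by the inputs.

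In counts, the planned split is "thirty of which will be randomly allocated to the therapy arm and thirty to the TAU arm". If there were 0.5 true events per participant (assumed), each arm would have 15. With s = 0.7 and q = 0.5, TAU would show 15 × 0.7 = 10.5 and CBTp 15 × (0.7 + 0.3 × 0.5) = 12.75, a gap of about two events.

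**3. Allowing for the therapy period**

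Sessions can only pick up events that happen while therapy runs. Assume that sessions span the first 2 of 12 months and that events are spread evenly. Then q over the year is 0.5 × 2/12 = 0.083.

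- s = 0.9: 1 + 0.083 × 0.1/0.9 = 1.01.
- s = 0.6: 1 + 0.083 × 0.4/0.6 = 1.06.

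Over 12 months the excess falls to about 1% to 6%. Events clustered soon after admission would raise it, and for the 2-month count alone the figures in part 2 could apply.

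**With common sources only**, q drops out of the formula and the ratio is 1.00 under equal true rates.

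**The case against.** The strongest reply is that a common source is already named. The record-based count covers serious incidents and adverse events without regard to arm, and session monitoring can be read as an individual safety check that never enters the comparison. For serious or well-documented events, such as harm to self or others, records may miss little, and the excess would then be close to zero. This stands as a limit on the size of the problem. It does not remove it, because the protocol does not say that the summary uses records alone, and it lists serious adverse events with the therapy data without saying how the two are combined. Records could also inherit the imbalance if therapists write what they hear into the notes, on which the protocol is silent.

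A second reply is that no safety comparison is specified. The regression adjusts for a baseline value, and Table 1 shows no baseline adverse event measure, so that model does not readily fit. This is fair. A descriptive table by arm is still likely, and it would carry the same distortion.

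A third reply is that the source of the adverse event table is a detail for the analysis plan or the full protocol, neither of which is shown. The choice of source for the table may be left there. The unequal collection, however, is stated in this document.

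A fourth reply is that any excess would count against CBTp and so could not give false reassurance about harm. That is correct, and it is a reason to treat the matter as modest.

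**Conclusion.** The point holds in conditional form. Collection is more frequent in the CBTp arm, by an unblinded route for which no TAU counterpart is described. If events from that route are pooled into the by-arm summary, CBTp counts will probably be inflated, chiefly for non-serious events and while therapy is under way.

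The documents do not fix the size. Taking 60% to 100% capture by common sources and half of the rest caught at sessions, the spurious excess lies between zero and about a third. Spread over 12 months with a two-month therapy period, it is about 1% to 6%.

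A reader might infer that the safety comparison is biased as planned, or that 3 against 9 to 11 occasions measures the bias. The documents support neither reading. No safety comparison is laid down, a source that appears common to both arms is available, and occasions do not translate directly into counts. This is an inexpensive improvement to a pilot whose analysis is mainly descriptive, not a flaw that undermines it.

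**What to change.** Leave session monitoring as it is for individual safety, and make three changes around it:

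- Add a source field to the adverse event form (clinical record, scheduled follow-up or therapy session), completed for every event.
- State that the between-arm adverse event table uses only sources applied identically in both arms: the clinical-record review and the 2-, 6- and 12-month collections.
- List events known only from therapy sessions separately, outside the comparison, so that nothing goes unreported.

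The cost is one form field and one extra table. A few CBTp events will sit outside the between-arm comparison. In return, the pilot will show how many events the sessions add, which is useful when planning safety collection in the larger trial.
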